## Abstract

**Introduction:**

Inadequate production of the essential stress hormone, cortisol, results in adrenal insufficiency (AI), which is associated with significant morbidity and mortality. The current standard diagnostic test for AI is the Short Synacthen Test (SST), but this is both invasive and resource-intensive, involving cannulation and blood sampling. A novel formulation, Nasacthin, has been developed in which the same Active Pharmaceutical Ingredient can be delivered intranasally, with the resultant glucocorticoid levels either measured in serum, or in saliva samples to render the test non-invasive, thus creating a potentially more cost-effective test. The Salivary Test of Adrenal Response to Liquid Intranasal Tetracosactide (STARLIT-3) study aims to determine the diagnostic utility of the test in patients with AI.

**Methods and analysis:**

STARLIT-3 is a randomised 2-way crossover trial which aims to collect data from 32 AI patients allocated to receive both Synacthen and Nasacthin in a random order across two study visits. Paired blood and saliva samples will be collected from participants at baseline, and then at 30 and 60 min after drug administration. Glucocorticoid levels in study samples will be quantified with the aim to determine whether the Nasacthin test is able to correctly diagnose patients with AI by estimating the positive percent agreement with the standard SST using serum cortisol at 30 and 60 min. Data on any reported harms and on the acceptability, usability and tolerability of the Nasacthin test will also be collected.

**Ethics and dissemination:**

The study and subsequent amendments have been reviewed and approved by South Central—Hampshire A Research Ethics Committee. Results will be published in peer-reviewed journals and presented at national and international conferences. Plans for dissemination of results to trial participants will be developed in collaboration with patient and public involvement and engagement groups.

**Trial registration number:**

ISRCTN26461337.

STRENGTHS AND LIMITATIONS OF THIS STUDYRobust study design that will produce data as agreed with the Medicines and Healthcare products Regulatory agency (MHRA) to support the regulatory approval of Nasacthin as part of a series of related studies.Randomised two-way crossover design enables direct within-participant comparison of Short Synacthen Test and Nasacthin test in adrenal insufficiency (AI) patients.Inclusion of detailed safety, acceptability, usability and tolerability data supports evaluation of practical implementation in clinical settings.Small sample size (32 participants completing both visits) limits statistical power to investigate any potential impact from factors such as ethnicity, body mass index, types of AI etc.Exclusion of children <4 years of age (unable to participate due to salivary collection techniques), and coryzal illness, hay fever etc. (which could potentially influence the absorption of nasal drug) could restrict applicability.

## Introduction

### Background and rationale

 Adrenal insufficiency (AI) is a potentially life-threatening endocrine disorder characterised by inadequate adrenal gland cortisol production due to endogenous or iatrogenic causes. Primary AI originates from adrenal gland dysfunction and direct impairment of cortisol production. The term central AI is associated with impaired production or action of adrenocorticotropic hormone (ACTH)^1^ and collectively describes both secondary AI (specifically related to pituitary defects) and tertiary AI (of hypothalamic origin). The most prevalent form is iatrogenic tertiary AI owing to sustained exogenous glucocorticoid use and resultant hypothalamic suppression.^2^

Diagnosis of AI is frequently delayed due to non-specific signs and symptoms at presentation. This risks the development of an acute life-threatening complication, adrenal crisis. Timely identification of AI is therefore essential.

In current clinical practice, the most performed diagnostic test for AI is the Short Synacthen Test (SST).^3 4^ This involves either intravenous (IV) or intramuscular injection of Synacthen (active ingredient tetracosactide), a synthetic analogue of ACTH (ACTH1-24), to simulate endogenous production from the adrenal cortex. The resulting serum cortisol response is quantified at 30±60 min. There is increasing demand for SSTs across all healthcare sectors^3 4^ due to increased glucocorticoid prescribing. The test is time-intensive, labour-intensive and resource-intensive, requiring skilled personnel with an associated inpatient tariff,^5^ and venesection which can be distressing and painful, especially for children.^6^,^8^

Salivary glucocorticoid measurement provides a non-invasive and more patient-friendly alternative to serum cortisol measurement and is increasing in adoption in clinical practice.^5 9^ A strong association between serum cortisol and salivary cortisol has been demonstrated,^10^,^14^ and salivary cortisol is not affected by interference from circulating cortisol-binding proteins, such as albumin or corticosteroid-binding globulin. Late-night salivary cortisol measurement is already recommended in the diagnosis of Cushing’s syndrome,^11^ and both basal and stimulated morning salivary cortisol levels pre-Synacthen and post-Synacthen have been investigated in both healthy and patient populations as a potential approach to AI diagnosis.^15^,^18^

Rapid enzymatic conversion of cortisol in saliva to cortisone due to expression of 11β-hydroxysteroid dehydrogenase type 2 in salivary glands means that the concentration of cortisone is typically 4 to 6 times higher than that of cortisol in saliva^10 19^ and is detectable at low serum cortisol levels.^13 14^ Salivary cortisone has been found to exhibit a better and more linear correlation with serum total cortisol than salivary cortisol^13 14 20^ and, as such, salivary cortisone is generally considered the preferred salivary biomarker for AI diagnosis.^9^ A recent NICE evidence review recommended further research on the clinical and cost-effectiveness of salivary cortisone/cortisol for AI diagnosis.^21^

The Nasacthin test has been developed as a non-invasive alternative to the SST stimulation test. The tests both use the same active pharmaceutical ingredient, tetracosactide, but in Nasacthin this is combined with a mucoadhesive agent, chitosan, to aid nasal absorption, and is delivered intranasally via a spray. Resultant glucocorticoid levels (cortisol and cortisone) can be measured in serum, but to render the test needle-free, saliva samples can be collected to quantify the adrenal response.

Nasacthin has been trialled over four open-label multi-arm sequence-randomised crossover pharmacodynamics studies^22^ across which a total of 70 doses of Nasacthin were administered to healthy males and children of both sexes. In these studies, it was found to be reliably absorbed, demonstrating a comparable plasma cortisol response to the IV SST at 60 min (the optimal timing of salivary glucocorticoid sampling following stimulation with IV Synacthen^17^), and well-tolerated with no serious adverse event (SAE) reports. Any AEs recorded were anticipated following nasal drug administration and were mild with full and rapid resolution.

If successfully adopted into clinical practice, Nasacthin would provide a simpler, non-invasive, easy-to-administer alternative to the SST, that could be carried out at the point of need. This would offer the potential to reduce the length of time to diagnosis, helping to reduce missed diagnoses and deaths from adrenal crisis, and wean patients from steroids in a more timely manner. The Nasacthin test has the potential to provide a more streamlined and cost-effective clinical care pathway, with particular benefit to low and middle-income countries where testing in conditions such as tuberculosis (TB) and AIDS is impacted by prohibitively high costs of Synacthen testing.^23^,^25^

The Salivary Test of Adrenal Response to Liquid Intranasal Tetracosactide (STARLIT-3) study aims to demonstrate a comparative diagnostic performance of Nasacthin in an AI patient population to the reference standard SST routinely used in clinical practice. The related STARLIT-2 study, which closed to recruitment in April 2025, aims to provide a parallel comparison of the SST and the Nasacthin test in healthy volunteers, including men, women and children.^26^

## Methods and analysis

This trial methodology is reported in accordance with the standard protocol items: recommendations for interventional trials (SPIRIT) reporting guidelines.^27^

### Trial aims and objectives

The STARLIT-3 study is designed to demonstrate that adrenal function testing with Nasacthin investigational medicinal product (IMP) can be used to correctly diagnose patients with AI at a comparable level to the standard IV Synacthen test, primarily at 30 min post-IMP administration, but also after 60 min, the optimal timepoint for salivary glucocorticoid sampling.^17^

Data on any harms or unintended effects associated with the use of Nasacthin will also be collected, along with qualitative data from focus groups and questionnaires to explore the acceptability, usability and tolerability of Nasacthin administration in study participants and by healthcare professionals. A further exploratory objective will compare the serum cortisol, salivary cortisol and salivary cortisone responses at 30 and 60 min following Synacthen versus Nasacthin administration.

### Trial design

This is a randomised two-way crossover trial involving patients with AI across two participating study centres, Sheffield Children’s NHS Foundation Trust (Sheffield, UK) and Sheffield Teaching Hospitals NHS Foundation Trust (Sheffield, UK). The crossover design will ensure that any differences observed between the two IMPs are derived from within-participant comparison.

### Eligibility criteria

The study aims to recruit patients (aged 4–75 years) with known AI, confirmed with either a waking salivary cortisone of <7 nmol/L, basal cortisol <150 nmol/L or peak on SST <250 nmol/L at time of diagnosis or since. An additional waking salivary cortisone test may be requested to confirm eligibility in instances where a previous glucocorticoid result cannot be obtained. Patients with a confirmed pathology compatible with a diagnosis of AI (eg, Congenital Adrenal Hyperplasia or autoimmune Addison’s disease) and a basal cortisol 150–299 nmol/L or SST peak 250–299 nmol/L will also be recruited if eligibility is confirmed by a waking salivary cortisone of <7 nmol/L.

Eligibility will be confirmed in accordance with exclusion criteria listed in box 1.

Box 1Trial exclusion criteriaOngoing pregnancy.Use of oestrogen-containing hormonal contraception/hormone replacement therapy.Co-morbid condition requiring daily administration of a medication that interferes with the metabolism of glucocorticoids, including all oestrogens, loperamide, oral antifungals and opiates.Currently prescribed anti-epileptic medication, such as sodium valproate, phenytoin, clonazepam, nitrazepam, phenobarbital or primidone.Currently prescribed amphetamines, for example, lisdexamfetamine, dexamphetamine.Known and active protein-losing disorder, for example, enteropathy or nephrotic syndrome.Known clinical or biochemical evidence of hepatic or renal disease.Current uncontrolled active infection.Known or suspected alcohol dependence or drug misuse.Current smoker or vaper (or within 6 months of cessation).Recent (within last 1 week) liquorice ingestion (preparations containing glycyrrhizic acid only).History of known salivary gland or oral mucosa pathology or unable to produce a suitable salivary sample (eg, as a consequence of drugs that cause dry mouth).Previous severe allergic reaction or anaphylaxis, or adverse reaction to any antigen of adrenocorticotropic hormone (ACTH) or Synacthen.Participation in another clinical trial of an investigational or licensed drug or device within the last 3 months.Unable to comply with the requirements of the protocol.Any other significant medical or psychiatric condition that, in the opinion of the investigator, would preclude participation in the trial.Exclusions for Nasacthin (nasal investigational medicinal product) visits only (visit should be rescheduled):Active nasal symptoms, including coryzal symptoms within the last week, active allergic rhinitis (hay fever) symptoms currently requiring medication, or heavy nosebleed within the previous 48 hours.

### Sample size

A sample size of 30 participants completing both study visits has been calculated using SAS PROC POWER to provide >90% power to show a positive percent agreement (PPA) of >80%, assuming a 5% alpha and a 1-sided exact test. The overall sample size has been increased to 32 completed participants to allow for up to two participants who are not identified as having AI by the SST being excluded from the PPA calculation to ensure at least 30 remain for inclusion in the main analysis. To account for predicted attrition, the recruitment target has been set at 41 participants.

Participants will be asked to return for a repeat visit or will be replaced if unable to produce the requisite samples for a visit (eg, due to cannula failure or inability to produce sufficient saliva). An absolute minimum of 25 pairs of samples from participants with confirmed AI (re-assessed as part of the trial using the SST) would provide 80% power to demonstrate PPA >80%, using serum cortisol at 30 min, for the final primary endpoint analysis.

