#### Blind data review

While no formal interim analysis is planned, the trial statistician will perform a quality control check on cortisol and cortisone values derived from each batch of study samples throughout the data collection phase and prior to provision of the final dataset. Individual visit data will be treated as completely independent (no within-participant linkage across visits) with original participant ID numbers removed from the dataset to preserve blinding. Spaghetti plots of all timepoints within each visit will be created and grouped by endpoint—serum cortisol, salivary cortisol, salivary cortisone. Any anomalies noted will be explored and resolved prior to database lock.

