### Trial oversight

Sheffield Children’s NHS Foundation Trust is the study sponsor, and HHTU is responsible for trial implementation and management and will perform central and site monitoring in accordance with a sponsor-approved trial monitoring plan.

A trial management group (TMG) has been convened and meets regularly to oversee trial delivery and operations. An independent Trial Steering Committee (TSC), comprising two expert clinicians, a statistician, a trials methodologist and two PPIE representatives, will provide overall trial supervision and advice on behalf of the sponsor and project funder and hold executive power on key trial-related decisions. An independent data monitoring and ethics committee (DMEC), comprising two expert clinicians and a statistician, will monitor progress, review efficacy and safety data, and make recommendations to the TSC on study conduct and continuation where necessary.

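### Thirty-two completers secure 30 evaluable participants only if at most two pass the SST, and the stated floor of 25 hides lower power at 26 to 29

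*Protocol article*

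**What the plan says.** The Sample size section of the protocol article gives the basis: "A sample size of 30 participants completing both study visits has been calculated using SAS PROC POWER to provide >90% power". The test behind this figure is exact and one-sided at the 5% level, against a PPA of 80%. The section then moves the target to 32 completers "to allow for up to two participants who are not identified as having AI by the SST being excluded from the PPA calculation to ensure" that 30 stay in the main analysis. The recruitment target is 41, and the difference from 32 is attributed to predicted attrition. On replacement, the section says that participants will be asked back for a repeat visit or "will be replaced if unable to produce the requisite samples for a visit". It also names an absolute minimum of 25 sample pairs from SST-confirmed participants, said to give 80% power.

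Under Final analysis, the primary PPA uses only participants who fail the trial SST (serum cortisol ≤429 nmol/L) and have a 30 min serum cortisol after Nasacthin. Those who pass are only summarised.

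Under Eligibility criteria, entry can rest on a waking salivary cortisone <7 nmol/L, a basal cortisol <150 nmol/L "or peak on SST <250 nmol/L at time of diagnosis or since".

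**The concern.** The target is counted in completers, but the power statement needs completers who fail the SST. A participant who attends both visits, gives every sample and passes the SST counts towards the 32, leaves the primary analysis, and meets no replacement trigger that the article states. The qualifying result may date from diagnosis, and it need not be an SST, so some passes are possible. The article gives no pass rate behind the allowance of two.

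The size of the loss matters because an exact test on so few participants moves in steps. Going from 30 to 29 evaluable could cost much more power than one participant suggests. A reader would also take the floor of 25 to mean that any number from 25 upwards gives at least 80% power, and that needs checking.

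**Working it through.** **Inputs.** From the Sample size section: null PPA 0.80, one-sided exact test at 5%, 30 evaluable, 32 completers, an allowance of two passers, a target of 41 and a floor of 25. Two inputs are not given and are assumed: the true PPA (p1) and the SST pass rate among completers (q).

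**Step 1: reproduce the stated power.** The critical count r is the smallest value with P(X ≥ r | n, 0.80) ≤ 0.05. Power is P(X ≥ r | n, p1).

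- n = 25: r = 24 (attained level 0.027). Power is 80% at p1 = 0.967.
- n = 30: r = 28 (attained level 0.044). Power is 92.5% at p1 = 0.967.

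A single p1 of about 0.967 therefore reproduces both the figure above 90% at 30 and the 80% at 25.

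**Step 2: power between 25 and 30.** At n = 29, 27 agreements give P(X ≥ 27 | 29, 0.80) = 0.052, just over 0.05, so r stays at 28. Two disagreements are allowed only from n = 30.

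| Evaluable n | r | Disagreements allowed | Power, p1 = 0.967 | Power, p1 = 0.97 | Power, p1 = 0.975 |
|---|---|---|---|---|---|
| 25 | 24 | 1 | 80.1% | 82.8% | 87.1% |
| 26 | 25 | 1 | 78.9% | 81.7% | 86.3% |
| 27 | 26 | 1 | 77.6% | 80.6% | 85.4% |
| 28 | 27 | 1 | 76.4% | 79.5% | 84.6% |
| 29 | 28 | 1 | 75.2% | 78.4% | 83.7% |
| 30 | 28 | 2 | 92.5% | 94.0% | 96.2% |

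Worked example at p1 = 0.967:
- n = 29: 0.967^29 + 29 × 0.967^28 × 0.033 = 0.378 + 0.374 = 0.752.
- n = 30: 0.967^30 + 30 × 0.967^29 × 0.033 + 435 × 0.967^28 × 0.033² = 0.365 + 0.374 + 0.185 = 0.925 (unrounded terms).

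A third passer takes the count from 30 to 29, which lowers power by 92.5 − 75.2 = 17.3 points.

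**Step 3: chance of falling below 30.** If completers pass independently with probability q, this is 1 − P(X ≤ 2 | 32, q). At q = 2/32 = 0.0625: 1 − (0.127 + 0.270 + 0.279) = 0.323 (unrounded terms).

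**Step 4: average power.** Weight the power at each evaluable n by its binomial probability, with 32 completers and p1 = 0.967.

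| Assumed pass rate q | P(more than 2 of 32 pass) | Average power |
|---|---|---|
| 2% | 2.6% | 91% |
| 5% | 21% | 88% |
| 6.25% | 32% | 87% |
| 10% | 63% | 82% |

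**Step 5: spare places.** 41 − 32 = 9, and 9/41 = 22%. If all nine are lost to the predicted attrition, exactly 32 complete and no one is left to replace a third passer.

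**The case against.** The best defence is that nothing here is an error. The figure of 30 is expressly tied to an allowance of up to two passers, and with two or fewer it is correct. A reader might infer a contradiction or an arithmetic mistake, but the text supports neither. This is a planning assumption with no stated basis.

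A reader might also infer that many participants will pass and that the trial is underpowered. The documents do not show that. Entry thresholds (<150 basal, <250 peak, and up to 299 nmol/L only with confirmed pathology and a salivary result) lie far below 429 nmol/L. At a pass rate of 2% the allowance of two suffices with about 97% probability. The plan also foresees a shortfall: 32 completers leave at least 25 evaluable with probability 98.8% even at a 10% pass rate. Average power stays above 80% over the range shown. All this stands, and it limits the weight of the point.

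Nor can it be said that no one sees results during recruitment. The Blind data review would not supply the count as described, since "Individual visit data will be treated as completely independent (no within-participant linkage across visits) with original participant ID numbers removed from the dataset". But under Trial oversight the data monitoring and ethics committee (DMEC) "will monitor progress, review efficacy and safety data, and make recommendations to the TSC", so a route exists.

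Finally, the article condenses a full protocol that is not shown, and a fuller replacement rule may sit there. The point is confined to what the article states.

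The defence does not rescue the floor of 25. Under the PPA that yields the quoted 80% there, every count from 26 to 29 does worse.

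**Conclusion.** The point holds in a limited form. Thirty-two completers give 30 evaluable only if at most two pass the SST. If the true pass rate equalled the allowance itself (2/32), that condition would fail about one time in three. The cost in average power is moderate: from about 91% at a 2% pass rate to about 82% at 10%, at a true PPA of 0.967.

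The floor statement misleads, because power at 26 to 29 evaluable is 75% to 79% under the PPA that reproduces the article's own figures. That result depends on the PPA. At 0.97 only 28 and 29 fall below 80%, and at 0.975 or more none does. Both the PPA and the pass rate are assumptions here, since the article states neither, and passing is taken as independent between participants.

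**What to change.** 1. Define the recruitment endpoint as 30 participants with paired 30 min samples who fail the trial SST (≤429 nmol/L), in place of 32 completers.
2. Use any places left within the target of 41 to replace SST-passers. Have the DMEC statistician report only the number of SST-fail completers, without Nasacthin results. Replacement then depends on the reference test alone, and no Nasacthin outcome can steer it.
3. Whether or not items 1 and 2 are adopted, state the assumed true PPA and SST pass rate and make the guarantee of 30 conditional on at most two passers. Correct the floor statement to say that, under the PPA so stated (about 0.967 if it is the one behind the quoted figures), power at 26 to 29 evaluable is below the 80% quoted for 25.

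The cost is a wording change and a periodic count from an existing committee. The downside is that more of the 41 may have to complete, and spare places may not exist if attrition is as predicted. In that case item 3 is what remains. Items 1 and 2 help only if adopted before recruitment closes.

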### Recruitment

Potentially eligible patients with AI will be identified by clinical teams at participating sites and approached either during scheduled clinic appointments or by invitation letter or email. For potential participants under 16 years of age, the initial approach will be to a parent/legal guardian as proxy. Study posters with a QR code link to the study website will also be displayed in endocrinology outpatient clinics and endocrine daycare units. Expression of interest in trial participation can be made directly to the research team or online via a survey link accessed via the study information provided.

Age-appropriate study-specific information will be provided to interested participants and their families by the site research team in response to an expression of interest, or can be accessed via the study website https://hhtu.hull.ac.uk/starlit-3/#tab-10804. An additional Participant Information Leaflet has been developed specifically for parents/legal guardians. An Easy Read version is also available to support inclusion of patients with recognised learning impairment or additional needs who have the capacity to give consent.

Eligibility will be confirmed by the site Principal Investigator or other appropriately delegated clinician, and then informed consent will be received by an appropriately trained and delegated study clinician or research nurse prior to any participant-specific study-related activities.

